## Objective

The objective of the MINDUUDD study is to evaluate the effect of a mindfulness and self-compassion training programme on the levels of work stress and burnout in residents and tutors of Family and Community Medicine and Nursing. This study is based on the hypothesis that an abbreviated 4-session programme of mindfulness and self-compassion is at least as effective as the standard 8-session programme to increase mindfulness and reduce the levels of work stress and burnout of AP residents and tutors.

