## Methods/design

### Study design (Fig. 1)

The MINDUUDD study comprises an open-label, pragmatic, non-inferiority, multicentre, cluster randomised controlled trial with three parallel arms. The participating UUDDs will be randomised to one of the three study groups. Interventions will last for 8 weeks for one group (EG8) and 4 weeks (EG4) for the other. In both groups, there will be a follow-up at three months to check the maintenance of the programs’ effect. The control group (CG) will be reassessed 8 weeks after the start of the fieldwork.

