### Sample size

To calculate the sample size, we have drawn on a previous study [25], using as an outcome variable the mean FFMQ score [31]; accepting an alpha risk of 0.05 and a beta risk of 0.2, in a bilateral contrast, 38 subjects are required in each group to detect a difference ≥ 15 points in the FFMQ scale between both experimental groups (EG4 and EG8) and the CG. It is assumed that the common standard deviation is 20. A loss or withdrawal rate of 25% has been estimated [43]. Because this is a cluster randomisation study, we have considered the design effect. The design effect multiplies the sample size by a factor ranging from 1.5 to 3 to achieve the same power, depending on the relationship between intra- and intergroup variance [44]. Estimates of the intra-cluster correlation coefficient (ICC) in randomised clinical trials in AP are generally < 0.05 [45]. This ICC, for a cluster size of 15, results in a design effect corresponding to a factor of 1.7. Assuming this value, the final study sample size would be at least 130 subjects. One hundred and thirty-two (132) professionals will be included, 44 in each comparison group, 22 for each teaching unit.

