### Statistical methods

The descriptive statistics of baseline characteristics of study participants and of questionnaire results—both before and after the intervention—will include means, standard deviations and ranges, medians and interquartile ranges, or frequencies and percentages, according to the variables. The fit of quantitative variables to the normal distribution will be checked by the Kolmogorov-Smirnov test. Prior to testing the effectiveness of the intervention, appropriate statistical tests will be used to examine possible baseline differences between groups (age, sex, time worked, profession, year of residency, previous mindfulness training). A per-protocol analysis will be performed in which all subjects who have completed at least 6 of the 8 sessions in EG8, or 3 of the 4 sessions in EG4, will be considered. All signalment analyses will be intention-to-treat in order to control for non-random dropout effects. Patterns of missing values ​​will be inspected and, if applicable, replaced using appropriate statistical methods.

To compare pre- and post-intervention results, a bivariate analysis will be performed, using Student’s t-test or the Wilcoxon test to compare related samples. Pre-post differences in the results of the questionnaires between the groups will be compared using ANOVA for repeated measures. Finally, a multivariate analysis will verify the effect of the interventions, adjusting for presumably predictive and/or confounding variables. To accomplish this, a multilevel linear regression will be used. The level of statistical significance will be set at *p* < 0.05 for all statistics. The analyses will be performed with SPSS version 17.0 and MLwiN version 3.00 software.

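### Neither the three-arm ANOVA nor the multilevel regression is tied to the EG4 versus EG8 non-inferiority hypothesis, and the only stated rule, p < 0.05 for a difference, cannot establish it

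*Protocol article*

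**What the plan says.** The Study design section calls the trial an "open-label, pragmatic, non-inferiority, multicentre, cluster randomised controlled trial with three parallel arms". The Objective gives the hypothesis that "an abbreviated 4-session programme of mindfulness and self-compassion is at least as effective as the standard 8-session programme". That is a one-directional comparison of EG4 with EG8.

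The Sample size section powers something else. It seeks a difference of 15 FFMQ points "between both experimental groups (EG4 and EG8) and the CG", with SD 20, "accepting an alpha risk of 0.05 and a beta risk of 0.2, in a bilateral contrast".

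The Statistical methods section gives two between-group analyses. First, "Pre-post differences in the results of the questionnaires between the groups will be compared using ANOVA for repeated measures". Then "a multivariate analysis will verify the effect of the interventions, adjusting for presumably predictive and/or confounding variables", for which "a multilevel linear regression will be used". One significance level, p < 0.05, applies to all statistics. No comparison between particular arms is named for either analysis. The article states no non-inferiority margin and no confidence-interval rule.

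Under Intervention scheme, the control group gives data at two time points only. Under Data collection and data management, only EG4 and EG8 are reconvened at three months.

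**The concern.** The Objective and the Sample size section each pose questions about pairs of arms. A repeated-measures ANOVA across three groups, with no contrast named, is most naturally read as the group-by-time F test on 2 degrees of freedom. That test asks only whether all three mean changes are equal. A significant result can come from either programme beating control and says nothing specific about EG4 against EG8.

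The regression comes closer, because it can yield arm-by-arm effects. But the only rule attached to it is a test of difference. Under that rule, the absence of a significant EG4–EG8 difference could be taken as support for the short programme, and such an absence is not evidence of non-inferiority. The Discussion part of the Abstract links adoption of the abbreviated programme to this conclusion, so the basis for it should be fixed in advance.

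**Working it through.** **Inputs.** From Sample size: difference 15, SD 20, two-sided 5%, power 80%, loss 25%, 44 per arm. Assumed here: SD 20 applies to the change score (the plan gives it only as a common SD), and participants are independent. Power figures below are therefore illustrative. They ignore clustering and the fact that only six TUs supply the cluster-level degrees of freedom.

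**1. The plan's own figure.** n = 2(1.96 + 0.84)² × 20²/15² = 2 × 7.85 × 1.778 = 27.9, so 28 per group. Then 28/0.75 = 37.3, so 38, which matches the plan. (Without the loss step, 38 is also reached at alpha 0.05/3.) Either way it is a two-group comparison, not a three-group F test.

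**2. The three-arm F test at the post-intervention visit.** With two occasions, group-by-time is a one-way ANOVA on change, with λ = n Σ(μᵢ − μ̄)²/SD². Arm order is CG, EG4, EG8.

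- EG4 matches EG8, (0, 15, 15): mean 10, sum of squares 100 + 25 + 25 = 150.
- EG4 no better than control, (0, 0, 15): mean 5, sum of squares 25 + 25 + 100 = 150.

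Both give λ = n × 150/400. At n = 44, λ = 16.5 and power is 95.8% in both states. For any gain δ both sums equal 2δ²/3, so the equality does not depend on δ, the SD, n or a common design effect. It does need equal arms: with 40/38/33 completers, power is 92.8% and 90.1%.

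**3. Contrasts on the same data.** Simulation of 20,000 trials, 44 per arm:

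| Result | EG4 = EG8 | EG4 = CG |
|---|---|---|
| Overall F significant | 96.0% | 95.6% |
| EG4 significantly better than CG | 94% | 3% |
| EG4 significantly different from EG8 | 5% | 93% |

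The contrasts separate the two states; the F test does not.

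**4. The p < 0.05 rule applied to EG4 versus EG8.** The standard error is 20√(2/44) = 4.26. Suppose EG4 truly loses half of the 15-point gain, 7.5 points. Then 7.5/4.26 = 1.76, and the chance of a significant difference is about Φ(1.76 − 1.96) = Φ(−0.20) = 42%. About 58% of such trials would show no significant difference.

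**5. The same contrast read against a margin.** The article gives no margin, so a range is assumed. The table shows how often the lower 95% limit of EG4 minus EG8 lies above −margin (same simulation), and the n per arm for 80% power at one-sided 0.025, from 2 × 7.85 × 400/margin², before clustering and loss.

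| Assumed margin | EG4 = EG8 | EG4 = CG | n per arm |
|---|---|---|---|
| 5 | 21% | 0.0% | 252 |
| 7.5 | 41% | 0.01% | 112 |
| 10 | 64% | 0.1% | 63 |

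A contrast with a margin asks the right question. At 44 per arm its 95% half-width is about 1.96 × 4.26 = 8.4 points, or 8.4 × √1.7 = 10.9 with the plan's design effect of 1.7.

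**The case against.** **The regression is the concluding analysis.** The ANOVA is an intermediate step, and a multilevel model with a three-level group factor gives effects for single pairs of arms. This stands. A reader might infer that the ANOVA is the plan's only between-group test, and so that the plan cannot answer its own hypothesis. The document does not support that: the same section ends with a model that can produce every contrast needed.

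**Contrasts are analysis-plan detail.** Listing post-hoc comparisons is indeed commonly left to a fuller document, and the article does not rule them out. But the point is not a missing list. The named test and the stated rule, followed as written, do not bear on the stated hypothesis.

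**This is the missing margin under another name.** Partly. The EG4–EG8 interval needs a margin to give a verdict, so the two repairs go together. A margin alone would not change what the three-arm F test measures.

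**The F test is not three-arm throughout.** Correct. At three months only EG4 and EG8 are measured, so the equal-power argument applies to the post-intervention visit only.

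**The equality is general algebra, and the power figures are soft.** Both true. The argument rests on the equality, not on the level of power.

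A reader might also infer that a non-significant F would be reported as the two programmes working equally well. The article does not say so.

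**Conclusion.** The concern holds in a limited form. The plan ties neither the ANOVA nor the regression to the EG4 versus EG8 hypothesis or to the comparisons used for sample size. For equal arms, the overall F test is exactly as likely to be significant when EG4 matches EG8 as when EG4 is no better than control. With modestly unequal completers the two probabilities differ by under 3 percentage points in the case tried. Its significance therefore cannot bear on non-inferiority. A p < 0.05 rule for a difference in the regression cannot either: under the assumptions above, a 7.5-point shortfall would go undetected in about 58% of trials.

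The planned model is not unsuitable, and the hypothesis is not beyond its reach. The equality needs only equal arms and a common variance. The percentages assume SD 20 for change and independent participants, and should not be taken as the power of a valid analysis with six clusters.

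**What to change.** In Statistical methods, state that conclusions rest on contrasts of change from the planned multilevel model, with TU as the cluster, each with a 95% confidence interval:

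1. EG4 minus EG8 as the primary contrast, with non-inferiority judged by the interval against a margin that is prespecified and justified.
2. EG8 minus CG and EG4 minus CG, the comparisons that the Sample size section powers.

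State that the overall ANOVA F is descriptive and that a non-significant EG4–EG8 difference is not evidence of non-inferiority. At three months, only the EG4 minus EG8 contrast can be estimated.

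The cost is wording and a little analysis work, with no new data and no new model. Naming the contrast does not give it power: whether 44 per arm suffices depends on the margin chosen, as the table of assumed margins shows.

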### Quality controls, monitoring and follow-up

The educational programmes will be sent to the Spanish Health Quality Agencies for accreditation. Some sessions of the intervention groups will be randomly audio recorded, and external experts ([name], [name]) will assess that the intervention reliably follows the protocol and includes no other interventions. To assess the lasting effect of the intervention programs, a follow-up will be conducted through a third measurement three months after the end of the programmes. At that time, participants must respond to a questionnaire to check the extent to which they have continued to perform the mindfulness practices learned. They will also fill out the FFMQ, SCS, PSC, MBI and JSPE and will be asked again about their feelings of happiness, loneliness, and social and work isolation.

### Ethical considerations

Explicit authorisation will be requested from the management of the participating TU.

This research complies with the regulatory framework of reference to develop research projects in Spain (Law 41/2002 of November 14, regulating patient autonomy, and rights and obligations regarding information and documentation). Under Law 14/2007 of Biomedical Research, on the protection of personal data and guarantee of confidentiality, the data will not be used for purposes other than those expressed in the informed consent form. The confidentiality of the information will be preserved by following the necessary regulations; data recording will respect the precepts established in the current legislation on the protection of personal data. The study will conform to the standards of good clinical practice (art. 34 RD 223/2004; European Community Directive 2001/20/EC) and the protection of personal data (Regulation (EU) 2016/679 of the European Parliament and of the Council of 27 April 2016 on the protection of natural persons with regard to the processing of personal data and on the free movement of such data-GDPR).

### Dissemination policy

In the dissemination of the study, the publication rules of the Consolidated Standards of Reporting Trials (CONSORT) Statement for the reporting of cluster randomised trials will be followed (http://www.bmj.com/content/345/bmj.e5661.long).

## Discussion

This clinical trial aims to test the effectiveness of an abbreviated intervention against a standard programme and control in reducing stress and burnout in AP health professionals with teaching functions or in the postgraduate training period. Environmental evidence allows us to show the correlation between practices to cultivate mindfulness and self-compassion and the increase in resilience and psychological well-being of AP professionals [14, 46, 47], but the effect of these educational programmes has been little studied in those health professionals who combine their care activities with teaching, which usually entails more responsibility and work stress. Montero-Marín et al. [48] have shown that not all manifestations of burnout follow the typical pattern, as some subtypes hide within a flurry of activity, simulating a situation that may seem contrary to burnout. This situation may particularly occur in professionals with additional dedication to care activities, such as those teachers who perform voluntary and altruistic tutoring in our country. This characteristic makes our trial especially relevant because it will detect situations of hidden stress in an overloaded collective.

The expected results of this trial will be immediately applicable because, if our hypothesis is confirmed, an important group of professionals—tutors and residents— who form an essential collective of the Spanish SNS will benefit. In fact, incorporating the new evidence provided by this trial into the public health service will result in a better working environment, improving the quality of care and medical practice in routine patient care. National Health Services such as the SNS—subject to a significant care overload, even more pronounced in AP—require effective, shorter, and less costly interventions to improve accessibility, acceptability, and adherence. Mindfulness programmes can be offered if we can achieve profitable and realistic formats, adjusted to the characteristics and conditions existing in different target populations [15].

### Strengths and limitations

With the cluster randomisation method, we expect to minimise the Hawthorne effect (contamination bias) in the intervention study. Withdrawals or losses may occur, which would cause a selection bias because the characteristics of the non-responders may differ from those of the responders. Due to the experience of the instructors in charge, adherence is likely to be very high at the beginning of the training program, but the loss rate thereafter could reach 20%. To lessen this problem, the sample size was increased by 25% [44]. In addition, to minimise and control this effect, from the statistical point of view, an intention-to-treat analysis will be performed in addition to the per-protocol analysis.

The questionnaires to be used are validated for the Spanish population and will be filled out anonymously (an identification code will be assigned to match those completed before and after the intervention), so we expect no problems of validity and reliability leading to important information biases.

Although the CG does not perform any type of intervention, this study does not ensure that it will remain inactive throughout the fieldwork period, which may minimise the differences in the expected results when comparing this group with the intervention groups.

To verify that the effect of the intervention programmes lasts over time, a measurement will be taken three months after their application. Although the ideal would be farther in the future, this distance is not feasible given that some participants will conclude their training period soon after completing the study, making it difficult to recruit them afterwards.

Our aim is to incorporate and extend the practice of mindfulness to the work, teaching, and care activities of health professionals—counting on the evidence to be found in this trial and contribute to increasing and complementing the countless existing tests that have been applied in other work sectors, both public and private.

## Abbreviations

AP: Primary Care
CG: Control Group
EG4: Experimental Group, 4 weeks
EG8: Experimental Group, 8 weeks
EIR: Internal Nurse Resident
ICC: Intra-cluster correlation coefficient
MBSR: Mindfulness-Based Stress Reduction
MINDUUDD: Spanish acronym of the words Mindfulness (MIND) and Teaching Units (UUDD)
MIR: Internal Medical Resident
MSC: Mindful Self-Compassion program
SNS: National Health System
TU: Teaching Unit
